5.1 SECONDARY ENDPOINTS

- Mortality within 28 days after randomisation
- Proportion of patients admitted to the ICU within 28 days after randomisation
- Proportion of patients given tocilizumab as a rescue therapy within 14 days after randomisation
- Length of hospital stay in days
- Proportion of patients experiencing serious adverse events
- Proportion of patients with bacterial, fungal or opportunistic infections
- Changes in the laboratory parameters indicative of inflammation (CRP, IL-6, ferritin, and D-dimer) within 14 days after randomisation
- Viral clearance as assessed by nasopharyngeal RT-PCR at day 7.

Data collected will be entered into an electronic case report form; only study researchers will have access to these data and all the requirements in terms of data protection will be met.

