**3.2 SECONDARY OBJECTIVES**

To compare

- 28-day mortality
- the proportion of patients admitted to the ICU at 28 days
- the proportion of patients requiring rescue therapy with tocilizumab at 14 days
- the length of hospital stay in days
- changes in laboratory parameters, namely, levels of C-reactive protein (CRP), interleukin 6 (IL-6), ferritin and D-dimer (DD)
- the proportion of patients experiencing serious adverse events
- the proportion of patients with bacterial, fungal and opportunistic infections
- viral clearance as assessed by nasopharyngeal PCR.

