**4.3 CONTEXT AND DURATION OF THE STUDY**

For this study, we will invite consecutive patients with a diagnosis of pneumonia caused by SARS-CoV-2 (COVID-19) to participate, recruiting them in the emergency department or on a hospital ward.

The study was originally conceived in the Hospital Complex of Navarra, but it was envisaged that other centres would be able to join the study, at the discretion of the study coordinator, and it has been extended to Hospital Moisès Broggi (Sant Joan Despí, Barcelona), researchers from this second hospital having been involved in the development of this version of the study protocol.

Each patient will be followed up throughout their stay on a hospital ward and to at least 28 days after the date of randomisation, any patients discharged from hospital earlier being contacted by phone. Patients will be censored when they reach the primary endpoint, are lost to follow-up or die. Patient recruitment will finish when we reach a fixed sample size. It is expected that patients will start to be included and followed up as of April 2020 and that follow-up will be completed in May 2020 [In fact, recruitment began on 28 May 2020 and is expected to be completed by February 2021]. Interim analysis of the results is due to be performed when recruitment reaches 50% of the fixed sample size.

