**5.- OUTCOME MEASURES**

5.1 PRIMARY ENDPOINT

Proportion of patients with treatment failure up to 14 days after randomisation.

Definition of treatment failure:

1. Patient death or
2. ICU admission or
3. Start of mechanical ventilation or
4. Clinical worsening, defined as:
   - Decrease in PaO_2_ by ≥15% from baseline + laboratory or radiological progression or
   - SpO_2_ in ambient air falling to < 90% or PaO_2_ in ambient air to < 60 mmHg or PaO_2_/FiO_2_ < 300 mmHg.

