**6.- STATISTICS**

**6.1 SAMPLE SIZE**

It was estimated that 60 patients (30 in each arm) were needed to detect as significant (two-tailed type I error of 0.05 and a type II error of 0.2) an absolute difference of 25% in the primary endpoint between the groups: 35% in the control group and 10% in the intervention group. Assuming a loss to follow-up of 20%, it is necessary to recruit a total of 72 patients.

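### The censoring rule in section 4.3 is not limited to any analysis; applied to length of hospital stay, it would stop the count at treatment failure and lose what are probably the longest stays

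*Protocol*

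**What the plan says.** Section 3.2 sets out to compare "the length of hospital stay in days", and the secondary endpoints in section 5.1 list it as "Length of hospital stay in days". Neither place gives a start point, an end point or a treatment of deaths, and section 6.2 names no method for it.

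The one rule on observation time is in section 4.3: "Patients will be censored when they reach the primary endpoint, are lost to follow-up or die". It is not confined to any endpoint. The same paragraph opens with a wider promise: "Each patient will be followed up throughout their stay on a hospital ward and to at least 28 days after the date of randomisation".

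The primary endpoint in section 5.1 is "Proportion of patients with treatment failure up to 14 days after randomisation". Its definition of failure begins with "Patient death or" and "ICU admission or", and goes on to the start of mechanical ventilation and to clinical worsening. All of these except death leave the patient in hospital.

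The dependent variables in section 5 include the dates of ICU discharge, hospital discharge and death. The date of admission is among the independent variables.

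**The concern.** The censoring rule has no evident home in the primary analysis. That endpoint is a 14-day proportion, and section 6.2 compares it by a test of two proportions or by logistic regression, neither of which uses a censoring time. Length of stay is the only listed secondary endpoint that is itself a duration, so an analyst looking for a use for the rule would most naturally apply it there.

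Doing so would be wrong. A patient who goes to the ICU on day 3 and leaves hospital on day 16 would contribute 3 days, or would be censored at day 3. That censoring is informative, because patients who fail can be expected to stay longer than those who do not. The arm with more failures would then show a stay that is too short. If the treatment prevents failures, its benefit on stay is hidden or reversed; if it causes them, the stay is flattered.

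The other secondary endpoints are exposed too. A patient who worsens on day 3 and dies on day 20 would be out of observation before a death that the 28-day mortality endpoint is meant to count.

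**Working it through.** The protocol states no expected length of stay, so there is no figure of its own to reproduce. What can be checked is what the rule does to a comparison of stays.

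**Inputs**
- Failure rates, from section 6.1: "35% in the control group and 10% in the intervention group". Write fC = 0.35 and fE = 0.10.
- Assumed, not in the protocol, all in days from randomisation: stay without failure N = 8, stay with failure F = 16, day of failure T = 3.

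**Full stay**, mean = (1 − f) × N + f × F
- Control: 0.65 × 8 + 0.35 × 16 = 5.20 + 5.60 = 10.80 days
- Experimental: 0.90 × 8 + 0.10 × 16 = 7.20 + 1.60 = 8.80 days
- Difference, experimental minus control: −2.00 days

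**Stay cut at failure**, mean = (1 − f) × N + f × T
- Control: 0.65 × 8 + 0.35 × 3 = 5.20 + 1.05 = 6.25 days
- Experimental: 0.90 × 8 + 0.10 × 3 = 7.20 + 0.30 = 7.50 days
- Difference: +1.25 days

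**Why the sign turns.** The full difference is (fE − fC) × (F − N) = −0.25 × 8 = −2.00. The cut difference is (fE − fC) × (T − N) = −0.25 × (−5) = +1.25. The sign reverses whenever failures stay longer than non-failures (F > N) and failure occurs before the usual day of discharge (T < N).

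**Range.** Four sets of assumptions (N, F, T) were tried: (8, 16, 3), (8, 20, 4), (10, 15, 4) and (8, 12, 3). Each was run with failure rates of 35% against 10% and 35% against 20%. The full difference runs from −0.60 to −3.00 days and the cut difference from +0.60 to +1.50 days. The sign reverses in every case.

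**Censored instead of cut.** A simulation of 200,000 patients per arm used gamma-distributed stays (means 8 and 16 days), failure times with mean 3 days, failure rates of 35% and 10%, and a 28-day horizon.
- Full mean stay: 10.64 (control) against 8.75 (experimental), a difference of about −1.9 days.
- Kaplan-Meier restricted mean, censored at failure: 8.28 against 8.07, a difference of about −0.2 days.

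The sign holds, but most of the benefit disappears.

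**Deaths.** Death also ends a stay. Assume that survivors stay 10 days and that death rates are 5–15% in one arm and 2–5% in the other.
- Deaths on day 5 to 7: the arm with more deaths looks 0.09 to 0.50 days shorter.
- Deaths on day 14: it looks 0.12 to 0.40 days longer.

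**What a composite does.** Assume 30 patients with 10 failures, non-failures staying 8 days, surviving failures 20 days, and d deaths on day 10.
- Mean stay = (20 × 8 + (10 − d) × 20 + d × 10)/30: 12.0 days for d = 0 and 11.0 for d = 3. Three deaths look like an improvement.
- Days alive and out of hospital to day 28, with death scored 0 = (20 × 20 + (10 − d) × 8)/30: 16.0 for d = 0 and 15.2 for d = 3. The measure moves the right way.

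**The case against.** The strongest reply is that the protocol does not mean the rule this way. Section 4.3 does not mention length of stay, and its follow-up sentence covers the whole ward stay and at least 28 days. An ICU discharge date exists only after an ICU admission, which within 14 days is itself a failure, so data after failure are plainly collected. The 28-day mortality and ICU endpoints need them as well. This stands: full stays can be computed, and a careful analyst might do so. It does not remove the problem, because the rule is written without limit and nothing says which of the two statements governs.

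Second, censoring is not truncation. This also stands. A reader might infer that the rule reverses the result, but that follows only if stays are cut at failure. Under Kaplan-Meier censoring the benefit shrinks and keeps its sign.

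Third, how deaths enter a secondary endpoint is commonly left to an analysis plan, which is not shown here, and 28-day mortality would be reported alongside. A reader might infer that the missing death rule is itself an error, or that deaths always make an arm's stay look shorter. The documents support neither. Nor need deaths change the direction of the result. Take stays of 8 and 20 days, deaths on day 10, 35% and 10% failure in 30 patients per arm, and 3 deaths, all in control:
- Control: (19.5 × 8 + 7.5 × 20 + 3 × 10)/30 = 11.2 days
- Experimental: (27 × 8 + 3 × 20)/30 = 9.2 days

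The experimental arm is still 2.0 days shorter, against 3.0 days if none of the failures die.

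Finally, days alive and out of hospital is one valid choice among several; time to live discharge with death as a competing event is another. That is fair.

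**Conclusion.** The point holds as a defect in the censoring rule. As written, it would take patients out of observation at a non-fatal failure, contrary to the follow-up in the same section and to what the secondary endpoints need. Applied to length of stay at the planning failure rates, it turns a 2.0-day advantage into a 1.25-day disadvantage if stays are cut, or reduces an advantage of about 1.9 days to about 0.2 if they are censored by Kaplan-Meier. These sizes rest on assumed stays and failure times; only the failure rates come from the protocol. If the planned effect is real, the bias works against the experimental arm.

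It would go too far to say that the protocol cuts stays at failure, since it never applies the rule to this endpoint. The death effect is secondary: it is smaller under the rates tried and changes direction with the timing of deaths. It supports a composite measure but would not carry the point alone. The primary proportion is unaffected. For a secondary endpoint, the change is worth making but does not put the trial's main conclusion at risk.

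**What to change.** 1. In section 4.3, state that reaching the primary endpoint does not censor a patient for length of stay or any other secondary endpoint, and that follow-up continues to at least day 28 whether or not the patient has failed.
2. Compute stay to actual hospital discharge, from the dates already collected.
3. So that an early death does not count as a short stay, compare days alive and out of hospital to day 28 from randomisation, scoring 0 for death by day 28. A rank test such as the Mann-Whitney would serve. Report length of stay among survivors as description only.

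Step 1 is a change of wording, and step 2 needs no new data. Step 3 costs a less familiar unit. It is not quite wording only, because readmission dates are not among the listed variables, so any days of readmission must be asked about at the existing 28-day contact. The appendix reports 46 patients recruited and analysis under way, so the change should be dated, recorded as a change to a listed endpoint, and settled without sight of results by arm.

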**Dependent variables:**

- Death
- Date of death
- Rescue with an interleukin inhibitor, a biological therapy
- Date of rescue with interleukin inhibitor
- Need for mechanical ventilation (invasive or non-invasive)
- Date of mechanical ventilation (invasive or non-invasive)
- Need for high-flow oxygen therapy
- Date of high-flow oxygen therapy
- Need for ICU admission
- Date of ICU admission
- Date of ICU discharge
- Date of hospital discharge.

**Independent variables:**

Epidemiological data:

- Date of birth
- Sex.

Comorbidities:

- Exsmoker
- Smoker
- Type 2 diabetes mellitus
- Hypertension
- Hypercholesterolemia
- Kidney failure: stage 1-5
- Obesity: class 1-4
- Ischaemic heart disease
- Cerebrovascular disease
- Peripheral artery disease
- Chronic obstructive pulmonary disease
- Asthma
- Comorbidities as assessed by the Charlson index.

Clinical and hospitalisation-related parameters:

- Date of onset of symptoms
- Date of hospital admission.

Medication taken at home (prior to hospital admission):

- Metformin
- Dipeptidyl peptidase-4 inhibitors
- Sodium-glucose cotransporter-2 inhibitors
- Insulin
- Angiotensin-converting enzyme inhibitors- angiotensin receptor blockers
- Spironolactone
- Inhaled corticosteroids
- Hydroxychloroquine
- Others.

Medication given in hospital:

- Azithromycin, dates of starting and stopping treatment
- Lopinavir/ritonavir, dates of starting and stopping treatment
- Interferon beta-1b, dates of starting and stopping treatment
- Tocilizumab, dates of starting and stopping treatment
- Anakinra, dates of starting and stopping treatment
- Ciclosporin, dates of starting and stopping treatment
- Remdesivir, dates of starting and stopping treatment
- Colchicine, dates of starting and stopping treatment
- Other drugs, dates of starting and stopping treatment.

Baseline blood tests:

- SpO_2_/FiO_2_
- White blood cell count
- Lactate dehydrogenase (LDH)
- D-dimer
- Fibrinogen
- IL-6
- CRP
- Procalcitonin
- Ferritin
- Haemoglobin
- Platelet count.

Follow-up blood tests:

- SpO_2_/FiO_2_
- White blood cell count
- LDH
- D-dimer
- Fibrinogen
- IL-6
- CRP
- Procalcitonin
- Ferritin
- Haemoglobin
- Platelet count.

Radiological findings:

- Lobar pneumonia
- Multilobar pneumonia
- Radiological Severity Score for COVID-19.

Safety-related events (related to glucocorticoids):

- Decompensation of diabetes
- Infection
- Psychosis or mania
- Worsening of hypertension
- Dyspepsia
- Gastrointestinal haemorrhage
- Delay in viral clearance assessed by nasopharyngeal RT-PCR (7 days after the first RT-PCR)
- Others.

**5.- STUDY PROCEDURES**

**5.1 SCHEMATIC DIAGRAM OF THE STUDY**

**Figure 2. Flow of patients through the study**

[figure not shown]

Abbreviations: RT-PCR, reverse-transcription polymerase chain reaction; CRP, C-reactive protein; IL-6, interleukin 6; SpO_2_(AA), oxygen saturation in ambient air; PaO_2_(AA), partial pressure of arterial oxygen in ambient air; PaO_2_/FiO_2_, ratio of arterial oxygen partial pressure to inspired oxygen fraction; PCT, procalcitonin; MP, methylprednisolone; TCZ, tocilizumab.

**^(1)^** standard of care is administered at the discretion of the researcher and may include: lopinavir/ritonavir: 200/50 mg orally, 2 tablets q12h for 7 to 14 days; ± remdesivir: 200 mg loading dose intravenously on day 1, followed by 100 mg/day for 5 to 10 days; or no drug treatment.

**^(2)^** Single dose of TCZ, dose may be repeated 12-24 hours after the first dose in the event of worsening in laboratory parameters, in accordance with the recommendations of the Spanish Agency of Medicines and Medical Devices.

Patients in both arms will be given omeprazole concomitantly.

Note: This base regimen may be modified in both arms if there are changes in standard of care at the participating hospitals.

**5.2 RANDOMISATION**

After obtaining patient informed consent, the treatment strategy will be decided by block randomisation stratified by age into two groups (<75 and ≥75 years old). Randomisation will be performed with the randomizeR package in R software, using two blocks sizes (sized 4 and 6), with random permutation. The sequence will be generated by a unit (the Clinical Trials Platform of Navarrabiomed) independent of the researchers who will carry out patient recruitment and implement the protocol. These researchers will be blinded to the arm to which patients are to be allocated until the start of the intervention. The Clinical Trials Platform will inform the hospital pharmacy concerning the group allocation of each patient included in the trial.

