**6.2 STATISTICAL ANALYSIS**

Initially, univariate descriptive analysis will be performed: calculating measures of central tendency and dispersion (means, standard deviation and confidence intervals or median and interquartile range depending on the distribution of the data) for continuous variables and frequencies for qualitative variables with their corresponding confidence intervals for the overall rates. Kolgomorov-Smirnov tests will be used to assess whether the continuous data follow a normal distribution and therefore parametric tests can be used.

Subsequently, it will be assessed whether randomisation achieved balance between the two arms: comparing the means of quantitative variables using Student’s t or the Mann-Whitney U tests, as appropriate, and qualitative variables using the chi-squared test or Fisher´s exact tests. If the desired balance is achieved, the primary endpoint will be compared between the groups to test the null hypothesis (H0) that the proportions are equal, assuming that the statistic for assessing the differences follows a normal distribution with a mean of 0 and standard deviation of 1; otherwise, multivariate analysis will be performed using logistic regression to assess the risk of treatment failure, estimating the effect of the intervention as an odds ratio with the corresponding 95% confidence interval.

The analysis will be performed on an intention-to-treat basis

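### Randomisation is stratified by age, but the primary analysis does not name the age stratum; if age predicts failure, the default test is conservative and loses some power

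*Protocol*

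**What the plan says.** Protocol section 5.2 sets "block randomisation stratified by age into two groups", split at 75 years, "using two blocks sizes (sized 4 and 6), with random permutation". Allocation is therefore held close to equal within each age group.

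The primary endpoint (section 5.1) is binary: "Proportion of patients with treatment failure up to 14 days after randomisation".

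Section 6.2 makes the analysis depend on a check of baseline balance.

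- **If balance is judged achieved:** the failure proportions of the two arms are tested for equality, "assuming that the statistic for assessing the differences follows a normal distribution with a mean of 0 and standard deviation of 1". No stratum or covariate is mentioned.
- **If not:** "otherwise, multivariate analysis will be performed using logistic regression to assess the risk of treatment failure", reported as an odds ratio with 95% CI. The covariates are not listed.

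Neither branch names the age group used in the randomisation.

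**The concern.** Stratified blocks keep the arms alike in age, so differences in failure risk between age groups contribute little to the difference between arms. The ordinary two-proportion standard error does not know this. It counts the between-age-group variation as if patients had been allocated without regard to age. If age predicts failure, the statistic then has a variance below 1, and the standard normal reference that section 6.2 assumes is too wide for it.

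The two-branch rule does not rescue this. Stratified blocks tend to balance age, so age itself will seldom trigger the adjusted branch. The design leans towards the branch that leaves age out.

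What is at stake is power, in a trial with little to spare.

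**Working it through.** **Inputs from the protocol.** Two age strata and blocks of 4 and 6 (section 5.2). Failure rates of 35% and 10%, 30 patients per arm, "two-tailed type I error of 0.05 and a type II error of 0.2" (section 6.1).

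**Inputs not in the protocol, so assumed.** The share w aged 75 or older (10-30%) and the strength of the age effect. The latter is given either as an odds ratio for failure or as a gap d in failure rate between the age groups.

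**Step 1: the plan's own power.** Pooled two-sided formula, mean rate 0.225:

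[0.25·√30 − 1.96·√(2·0.225·0.775)] / √(0.35·0.65 + 0.10·0.90) = (1.369 − 1.157) / 0.563 = 0.376, and Φ(0.376) ≈ 64.7%.

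The same formula needs 43 per arm for 80%, so the stated 60 patients do not reproduce. That is a separate problem. It matters here only as the baseline from which power is gained or lost.

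**Step 2: size of the mismatch in closed form.** With near-equal allocation within strata and no treatment effect, the true variance of the difference divided by the variance the z-test assumes is about

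r = 1 − w(1 − w)d² / [p(1 − p)],

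and the actual two-sided error is 2·[1 − Φ(1.96/√r)].

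For w = 0.30 and p = 0.225, where p(1 − p) = 0.1744:

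| Age odds ratio | Rates <75 / ≥75 | d | r | √r | Actual error |
|---|---|---|---|---|---|
| 2 | 0.187 / 0.315 | 0.128 | 1 − 0.0034/0.1744 = 0.980 | 0.990 | 4.8% |
| 4 | 0.147 / 0.408 | 0.261 | 1 − 0.0143/0.1744 = 0.918 | 0.958 | 4.1% |
| 10 | 0.098 / 0.521 | 0.423 | 1 − 0.0376/0.1744 = 0.785 | 0.886 | 2.7% |

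**Step 3: simulation with permuted blocks of 4 and 6 within strata, N = 60.** CMH is the Cochran-Mantel-Haenszel test over the two age groups.

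- **Type I error of the z-test, 15-30% aged 75 or older:** about 5% with no age effect or an odds ratio of 2, 3.9-4.3% at 4, and 2.3-3.2% at 10. At a 30% share CMH gave 4.7%, 4.8% and 4.9% for odds ratios of 2, 4 and 10.
- **Power for 35% vs 10%, 30% share:** z-test 66 / 68 / 68% and CMH 66 / 70 / 75% at odds ratios of 2 / 4 / 10, a gain of 0 / 2 / 7 points. At a 15% share the gain is about 0 / 2 / 6 points. Across repeated runs the gain at an odds ratio of 10 is 5-8 points.

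**Step 4: a second parametrisation** (overall rate 35%, share 10-30%).

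- With a 20-point gap between age groups, z-test error at N = 60 is 4.3-4.7% and the power loss is 0-1 point.
- With a 40-point gap, z-test error at N = 60 is 3.2-4.5%. Power is 67-68% for the z-test against 69-71% for CMH.
- At N = 72 with a 40-point gap, power is 74-76% against 78-79%.

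**Step 5: where the loss arises.** At N = 60, 30% share and a 40-point gap, with no treatment effect, the estimated difference has a standard deviation of 0.114 whether or not the analysis is stratified. The unstratified standard error averages 0.121. The estimate is not noisier; its standard error is overstated.

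**The case against.** The best defence is that an unstratified test after stratified randomisation does not exceed its nominal error, so nothing is invalid, and that covariates are often left to an SAP, which is not at hand here. The first part stands. The second stands for the logistic branch, where age group could still be added. It does not cover the default branch, because section 6.2 already names that comparison and its reference distribution.

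The size can also be challenged. The protocol gives neither the share aged 75 or older nor failure rates by age. An odds ratio of 10 at a 30% share means control failure of about 20% in younger and 71% in older patients, which nothing in the protocol supports. With a weak age effect the gain is nil. This stands, and the larger figures should be read as an upper end.

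A reader might also infer four stronger things that do not follow:

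- **That the error rate is wrong in the harmful direction.** It is not. The departure is conservative, and it arises only if age is prognostic.
- **That the plan's confidence interval is wrong.** Section 6.2 attaches a treatment-effect interval only to the logistic odds ratio, so there is no unadjusted interval to criticise. A hypothetical unstratified interval for the risk difference covered 93.8-96.3% with no treatment effect, and exceeded 95% only with a 40-point gap between age groups.
- **That precision of the estimate is wasted.** Step 5 shows that its spread hardly changes.
- **That stratifying repairs the sample size.** At N = 60 even the odds ratio of 10 reaches only about 75%.

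**Conclusion.** The point holds in a limited form. The default primary test omits the stratification factor, and the fallback model does not name it. If age predicts failure, the test is conservative and gives up about 0, 2 or 5-8 points of power at age odds ratios of 2, 4 or 10 (N = 60, 15-30% aged 75 or older, all of these age inputs assumed). If age does not predict failure, the two analyses are practically equivalent.

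This is a worthwhile improvement of modest size, not a threat to validity. It ranks below two other matters in the same sections: choosing the primary analysis by a baseline balance check, and a sample size that gives about 65% power where 80% is stated.

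**What to change.** In section 6.2, state that the primary endpoint will be analysed stratified by the age group used at randomisation, whatever the baseline balance check shows: a Cochran-Mantel-Haenszel test over the two strata, with the Mantel-Haenszel risk difference and its 95% CI. Keep the unstratified two-proportion comparison as a sensitivity analysis. If the logistic model is retained as a supporting analysis, name age group as a covariate.

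The cost is one or two sentences. No new data are needed, since the stratum is known at randomisation and date of birth is collected. With no age effect the change costs less than a point of power. It also supplies the effect interval that the default branch lacks. The shortfall against 80% power needs its own correction.

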**4.- METHODS**

**4.1 STUDY DESIGN**

This is to be a phase 3 double-blind parallel-group randomised clinical trial:

1. Experimental group: standard of care + pulsed glucocorticoids versus
2. Control group: standard of care

The standard of care will consist of the treatment provided following the standard protocol at the time in the hospital. This may be updated during the course of the study.

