**5.3 INTERVENTION**

During the randomisation, patients with be randomly allocated to the experimental or control group (Figure 2):

- 1. Experimental group: standard of care at the discretion of the researcher, including lopinavir/ritonavir (200/50 mg orally, 2 tablets q12h for 7 to 14 days) ± remdesivir (200 mg loading dose intravenously on day 1, followed by 100 mg/day for 5 to 10 days), or no drug treatment, plus pulsed methylprednisolone (120 mg/day intravenously on days 1, 2 and 3).
  2. Control group (standard): standard of care at the discretion of the researcher, including lopinavir/ritonavir (200/50 mg orally, 2 tablets q12h for 7 to 14 days) ± remdesivir (200 mg IV on the first day, followed by 100 mg/day for 5 to 10 days), or no drug treatment, plus placebo* (intravenously on days 1, 2 and 3).

*Note: placebo consists of 100 ml of 0.9% sodium chloride.

The doses of methylprednisolone (120 mg IV) or placebo (NaCl 0.9% IV) will be prepared and dispensed by the hospital pharmacy. Only the staff responsible for preparing the medication will know patient group allocation. That is, neither the researcher nor nurses administering the treatment will know the content of the bags supplied.

Patients in both groups will be treated with tocilizumab if at any point the following are observed:

- Decrease in PaO_2_ ≥15% from baseline + laboratory or radiological deterioration and/or
- SpO_2_ in ambient air falling to < 90% or PaO_2_ in ambient air < 60 mmHg or PaO_2_/FiO_2_ below 300 mmHg not explained by any other condition.

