**APPENDIX IN RESPONSE TO THE MEASURES TAKEN BY THE SPANISH AGENCY OF MEDICINES AND MEDICAL DEVICES (AEMPS) REGARDING CLINICAL TRIALS OF HYDROXYCHLOROQUINE FOR COVID-19**

After the notification received by the researchers of the CORTIVID trial (EudraCT number: 2020-001827-15, Name of sponsor: Navarrabiomed-Fundación Miguel Servet) on 15 July 2020 and in accordance with the measures adopted by AEMPS on 22 June 2020 regarding clinical trials of hydroxychloroquine in COVID-19, the use of this drug in the CORTIVID trial was halted, as was the recruitment of patients on the drug. The design of the trial was modified accordingly, by amendment of the protocol to that detailed in this document.

The trial is currently in the active recruitment stage, with five patients having been included across two hospitals. [At the time of submission of this protocol for publication, 46 patients have been recruited and analysis is ongoing.]

We consider that the CORTIVID trial continues to be warranted and remains relevant in the current circumstances for the following reasons: 1) use of an active ingredient (methylprednisolone) and a different regimen (short three-pulse regimen) from that used in the RECOVERY trial; 2) research into the efficacy and safety of glucocorticoids in a clinical scenario that also differs from that considered in the RECOVERY study (patients with SARS-CoV-2 pneumonia not requiring oxygen but with poor prognostic factors); and 3) the possibility of confirming some of the findings of the RECOVERY trial in a double-blind randomized placebo-controlled study.

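### Allocation is stratified by age only in a trial with hospital-specific background care, and the primary comparison ignores hospital: chance imbalance in hospital mix is likely and cheap to handle in the analysis

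*Protocol*

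**What the plan says.** **Allocation.** Protocol section 5.2 describes "block randomisation stratified by age into two groups (<75 and ≥75 years old", "using two blocks sizes (sized 4 and 6), with random permutation". Age is the only stratification factor named.

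**Hospitals.** Section 4.3 says of further sites that "it was envisaged that other centres would be able to join the study", and that "it has been extended to Hospital Moisès Broggi (Sant Joan Despí, Barcelona". The appendix on the medicines agency's hydroxychloroquine measures describes recruitment "with five patients having been included across two hospitals". A bracketed update there gives 46 recruited and analysis under way when the protocol was submitted for publication.

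**Background care.** Section 4.1 defines standard of care as the "treatment provided following the standard protocol at the time in the hospital". The note to Figure 2 adds: "This base regimen may be modified in both arms if there are changes in standard of care at the participating hospitals". Section 5.3 describes it as "standard of care at the discretion of the researcher", ranging from antivirals to no drug treatment.

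**Analysis.** Section 6.2 first tests baseline balance. If balance is found, the two proportions are compared directly; if not, logistic regression is used. Neither hospital nor the age stratum is named. The list of independent variables in section 5 covers demographics, comorbidities, medication, blood tests, radiology and safety, but not hospital.

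**The concern.** The protocol ties co-treatment to the hospital and then leaves hospital out of both the allocation and the stated analysis rule. Blocks within age groups balance the arms over the whole trial. They do not balance them within a hospital unless lists are kept by site, which the protocol does not say.

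In a trial of 72 patients, one arm can end up with noticeably more patients from one hospital. If failure risk differs between hospitals, the observed treatment difference then carries part of the hospital difference. The rule in section 6.2 would not catch this: a variable that is not listed is not tested, so it cannot trigger the adjusted analysis.

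**Working it through.** **Inputs from the protocol.** 72 recruited, 60 evaluable, failure 35% against 10% (section 6.1); blocks of 4 and 6 and two age strata (section 5.2); two hospitals (section 4.3); 46 recruited (appendix).

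**Assumptions not in the protocol.** One list per age group shared by both hospitals; second-hospital share of one third to one half (20% to 50% where stated); 20% aged 75 or over; age unrelated to hospital; where outcomes are simulated, failure risk of 25% and 45% at the two hospitals.

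The protocol gives no figure for hospital imbalance, so there is none to reproduce.

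**Step 1: imbalance at the second hospital.** Simulated trials of 72 patients, permuted blocks of 4 and 6; ranges cover shares of one third to one half:

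| Allocation | Arms differ by 4 or more | Arms differ by 6 or more |
|---|---|---|
| Age strata only (as written) | 39-41% | 16-21% |
| Age by hospital from the start | about 1% | 0% |
| Age only for 46 patients, then age by hospital for 26 | 31-35% | 12-14% |

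Repeat runs move these figures by one or two percentage points. Switching after the first five patients gives 5-7% for a difference of 4 or more and under 1% for 6 or more.

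**Step 2: what these differences mean.** With 36 per arm, a difference of 4 is 4/36 = 11 percentage points in hospital share, and a difference of 6 is 6/36 = 17 points. The latter is 15 against 9 if the second hospital has 24 patients, or 21 against 15 if it has 36.

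**Step 3: effect on the estimate.** Shift = difference in hospital share × difference in failure risk between hospitals. At 15 points of share and an assumed 20 points of risk, 0.15 × 0.20 = 0.03. The standard error of the planned difference at 36 per arm is √[(0.35×0.65 + 0.10×0.90)/36] = √(0.3175/36) = 0.094. The shift is 0.03/0.094 = 0.32 standard errors, against a planned difference of 25 points.

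**Step 4: error rates of the unadjusted test.** Over second-hospital shares of 20% to 50% and 60 or 72 patients, the mean imbalance is about zero and the null rejection rate with age-only strata is 4.9% to 5.4%. With hospital strata and the same unadjusted test it is 4.2% to 4.5%. At 60 patients, half at each hospital, with failure averaging 35% against 10%, power is 0.67 under both schemes. These runs use the plain two-proportion test and do not model the switch to regression after balance tests.

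**Step 5: precision.** At 72 patients and a 35% share, the standard deviation of the estimated difference is 0.1095 with age-only strata and 0.1072 with age-by-hospital strata, a ratio of 1.02.

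**Step 6: events available for adjustment.** 36 × 0.35 + 36 × 0.10 = 16.2 expected failures.

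**The case against.** Blocked randomisation without centre strata is valid, and few strata is a reasonable choice for 72 patients when more centres may join. The documents contain no error of arithmetic here and no contradiction. All of that stands.

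Several stronger readings are tempting and are not supported:

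- **That the result is biased.** The imbalance is random with mean zero, and type I error stays near 5%.
- **That ICU practice differs between the hospitals and distorts the endpoint.** No section says so. The composite in section 5 also counts fixed oxygenation thresholds, which many deteriorating patients may meet before ICU admission. Only co-treatment is tied to the hospital in the text.
- **That one shared list was certainly used.** Section 5.2 does not describe how lists are organised by site. Naming age as the only factor makes a shared list the natural reading, but it is an inference.
- **That new lists would now remove the problem.** After 46 patients they hardly change it.

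Covariates are often left to a statistical analysis plan, which may name hospital. That limits the point, but section 6.2 already fixes an unadjusted comparison when balance is found, and it is this rule that needs changing. Co-treatment is recorded with dates, which helps description; these are post-randomisation data and do not replace a baseline hospital variable. Co-treatment also varies by researcher and over time, which hospital strata would not fully balance. Finally, about 16 events leave little room for model terms, which favours a simple stratified estimate over a larger regression.

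**Conclusion.** The point holds as one of conditional imbalance and modest loss of precision. If one list per age group serves both hospitals, and one third to one half of patients come from the second, the arms differ there by 4 or more patients in about 40% of trials and by 6 or more in 16-21%. A 15-point difference in hospital share moves the estimate by about 3 points if failure risk differs by 20 points between hospitals; that risk difference is an assumption.

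This does not threaten the validity of the trial, and the documents do not support calling the comparison biased. It is worth acting on because section 6.2 ignores the randomisation stratum, would not detect a hospital imbalance on the stated variable list, and can be corrected at little cost for every patient already randomised.

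**What to change.** 1. Add hospital to the baseline variables in section 5, and report it by arm.
2. In section 6.2, make the primary comparison stratified by age group and hospital, for example a Mantel-Haenszel risk difference with its 95% confidence interval, whatever the balance tests show.
3. State in advance how small strata are pooled. With 20% aged 75 or over, 72 × 0.20 = 14.4 patients fall in that group; with one third at the second hospital, only 14.4/3 = 4.8 of them are expected there. A stratum with no patients in one arm contributes nothing.
4. State in section 5.2 whether lists are kept by hospital. If they are, the imbalance largely disappears and only the analysis change remains.
5. Optionally, issue age-by-hospital lists for any patients still to be randomised. The time for this was when five were included and 72 − 5 = 67 remained; with 72 − 46 = 26 left, the gain is small.

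The cost is one recorded variable and a short amendment to the analysis text. The downside is sparse strata with about 16 expected events. The change should be fixed before anyone analysing the data sees outcomes by arm. The appendix reports analysis as ongoing, so if that point has passed, the stratified result should be labelled as added later.
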